#### Secondary outcomes

Key secondary outcomes include changes in sub-scores of SF-12 (physical and mental health) [29] and EQ-5D (mobility, self-care, usual activities, pain/discomfort, and anxiety/depression) [30]. Other secondary outcomes are health variables independently associated with hearing loss, including physical functioning (ADLs, IADLs) [31], chronic diseases, cognitive function (MMSE) [32], depressive symptoms (CES-D) [33], social support (LSNS) [34], hospitalizations, and falls, as well as the direct and indirect medical costs and loss of productivity in the study duration.

#### Hearing outcomes

Participants are required to receive pure tone audiometry at the thresholds of 0.5, 1, 2, and 4 kHz to derive accurate hearing data. Besides pure tone audiometry, standardized questionnaires like Hearing Handicap Inventory for the Elderly—Screening version (HHIE-S) [35], combined with participants’ self-reported hearing status, will be gathered to supplement the objective hearing data. For participants randomized to the hearing intervention group, audiologic outcomes to verify the intervention effects, such as the International Outcome Inventory for Hearing Aids (IOI-HA) [36], are gathered semiannually post-randomization.

#### Covariates

Sociodemographic factors such as age, gender, residency, family information, socioeconomic status, and other clinical factors are collected at baseline and the follow-up survey.

### Sample size

Power calculations showed that 404 (202 in each group) participants are required in each group to obtain 80% statistical power with a 5% significance level and to detect a 0.28-SD difference in the mean change from baseline in quality of life score to 20-month follow-up [37]. To account for drop-in (uptake of hearing aids in the control group) and drop-out (discontinuation of hearing aid use in the treatment group), 464 persons are included, of which 232 are in the intervention group and 232 in the control group.

### Recruitment

Our recruitment will last 1 month, from July 1 to 31, 2019. Adults with untreated hearing loss will be recruited according to the list of people with hearing loss provided by the hearing center of Linyi Disabled Persons’ Federation. Informed, written consent is obtained from all participants prior to participation.

### Randomization

Participants are randomized stratified by severity of hearing loss, so as to avoid uneven distribution of participants. A researcher who is not involved in data collection or analysis will use a random sequence generator (http://www.random.org) to allocate participants in a random sequence to the treatment or control group. In a separate room after completion of the baseline measurements, an independent researcher will tell participants to which group they have been allocated, thereby ensuring concealment of the identity and characteristics of participants.

### Blinding

Neither study participants nor researchers collecting outcome data can feasibly be blinded to randomization status. Precautions to minimize potential bias resulting from the lack of blinding include (1) blinding of participants to the study hypothesis, (2) use of standardized protocols for training of data collectors and assessment of study outcomes, and (3) masking of field working staff to block size, to avoid unintentional and possibly unconscious bias by study staff during data collection.

### Data collection

Standardized data forms or tablets are used to collect data with paper back up available in case of tablet failure. Participants will fill in all questionnaires in a separate room. To ensure that appropriate help and guidance can be given when needed, one of the researchers will present. Meanwhile, communication partners who communicate with participants on a daily or near-daily basis (e.g., spouse) are often a key to getting accurate results. Therefore, accompanying adults are also invited to join the study and contribute to the data.

To minimize data-entry errors, the questionnaires have inbuilt check-and-skip rules. And the questionnaires were tested on four participants beforehand, who found the questions understandable and possible to complete in 30–45 min. For participants who withdraw from the trial, any data collected up to the withdrawal date will be retained and included in the analyses. Data are collected at the local field prior to randomization (baseline T0), after 12 months (post intervention T1) and 20 months after baseline (follow-up T2). A SPIRIT flow diagram illustrates the data collection in the intervention group and control group (Table 2) [38].

**Table 2 Tab2:** Schedule of enrollment, interventions, and assessments

Timepoint	Study period							
	Enrollment −T_1_ −30 to −1 day		Allocation T_0_ day 0		Post-allocation T_1_ 12 months		Close-out T_2_ 20 months	
	T ^a^	C ^b^	T ^a^	C ^b^	T ^a^	C ^b^	T ^a^	C ^b^
Enrollment								
Eligibility screen	×	×						
Informed consent	×	×						
Allocation			×	×				
Intervention			×		×		×	
Assessments								
Socio-demographic data	×	×	×	×			×	×
Hearing outcome								
Pure tone audiometry			×	×			×	×
HHIE-S score			×	×			×	×
Self-reported hearing			×	×			×	×
IOI-HA score					×		×	
Quality of life (primary outcome)								
SF-12 score			×	×			×	×
EQ-5D score			×	×			×	×
Secondary outcomes								
Sub-dimension of SF-12			×	×			×	×
Sub-dimension of EQ-5D			×	×			×	×
Physical functioning (ADLs)			×	×			×	×
Physical functioning (IADLs)			×	×			×	×
Chronic diseases			×	×			×	×
Cognitive function (MMSE)			×	×			×	×
Depression (CES-D)			×	×			×	×
Social support (LSNS)			×	×			×	×
Hospitalizations			×	×			×	×
Falls			×	×			×	×
Medical costs			×	×			×	×
Loss of productivity			×	×			×	×

*Abbreviations: T*, treatment group; *C*, control group; *HHIE-S*, Hearing Handicap for the Elderly-Screening Version; *IOI-HA*, The International Outcome Inventory for Hearing Aids; *SF-12*, Short Form 12 Health Survey; *EQ-5D*, EuroQoL 5-Dimension; *ADLs*, activities of daily living; *IADLS*, instrumental activities of daily living; *MMSE*, Mini-Mental State Examination; *CES-D*, Center for Epidemiologic Studies-Depression; *LSNS*, Lubben Social Network Scale

### Data management

The data entry is double-checked for errors or omissions by an investigator blinded to the participants’ group allocation. For data coding, some measures such as range checks in data values are conducted. Then data shall be filed and stored in categories, and have multiple backups on different disks or recording media.

### Statistical analysis

In the statistical analysis, intention-to-treat (ITT) principle is applied with conservative estimates of missing data [39]. Participants’ characteristics will be summarized using descriptive statistics (mean, standard deviation, frequency). Analysis of variance or *t* tests are performed to compare means; Mann-Whitney *U* tests are used to compare variables with non-normal distribution. Baseline data will be used to investigate the characteristics of participants who discontinue or deviate from the trial and/or intervention. The magnitude of changes over time across study groups will be examined by a multiple imputation analysis of covariance model, so as to evaluate the intervention effect.

In addition, some variables such as socioeconomic status and social support may potentially affect the utilization of hearing rehabilitative services, so the interaction between socioeconomic status or social support with the hearing intervention can be analyzed to gain further results. The cost-effectiveness analysis is based on the cost of the intervention, effects in improving health-related quality of life, decreasing inpatient and outpatient visits, and saving healthcare costs and recovering productivity. By these means, we aim to explore the most cost-effective intervention strategy to improve the quality of life for people with hearing loss.

### Data monitoring

The principal investigator (PI) is responsible for the quality and integrity of data collected. During the period of recruitment, interim analyses will be supplied in strict confidence, which may include analyses of data from other comparable trials. In the light of these interim analyses, the PI will advise if the intervention has been proved, or different from expected. Then the PI will decide whether or not to modify the trial. Unless this happens, however, study staff will remain ignorant of the interim results.

### Adverse events

In our study, adverse events will be collected and recorded after participants have provided consent and enrolled, until the end of the study. If a participant experiences an adverse event after the informed consent is signed (entry) but the participant has not started to receive study intervention, the event will be reported as not related to our intervention. An adverse event that meets the criteria for a serious adverse event (SAE) will be reported to the institutional review board (IRB). And study personnel will document the circumstances.

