### Study interventions

Participants in the hearing treatment group are prescribed with hearing aids at baseline, while the control group with no interventions. Reinstruction in use of hearing aids is prescribed during booster visits held 12 months and 20 months post-randomization. Unscheduled interim visits may also be sporadically required (e.g., hearing aid malfunction). Participants in the control group will not have access to hearing aids. They will be asked to attend twice for this project: baseline and follow-up 20 months later.

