### Adherence

Adherence to the study intervention will be assessed at each study visit using questions designed to capture adherence in both the treatment and control groups. Strategies to promote adherence include:
Individual assessment and instruction.Participants are asked to bring a communication partner with them to the study visits.Participants who miss a scheduled meeting are contacted by telephone by study staff to encourage continued participation and to evaluate and overcome barriers to participation.

For the treatment group, it additionally includes:
Potential intervention benefits are structured given the participant’s level of hearing loss in order to ensure that participants’ expectations are reasonable and realistic.Participants are informed that they are allowed to keep the hearing aids for free if they complete all study visits.

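### Adverse events are recorded to study end in both arms on unequal contact schedules, so a by-arm table of all recorded events would tend to show more with hearing aids

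*Protocol article*

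**What the plan says.** Under Adverse events, the protocol article states that "adverse events will be collected and recorded after participants have provided consent and enrolled, until the end of the study". Serious events go to the institutional review board. Nothing there limits collection to one arm.

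The contact schedule is set elsewhere and differs by arm:

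- **Controls.** Study interventions says: "They will be asked to attend twice for this project: baseline and follow-up 20 months later". Table 2 agrees: controls have no entry at T1 (12 months).
- **Treated participants.** Study interventions says: "Reinstruction in use of hearing aids is prescribed during booster visits held 12 months and 20 months post-randomization". It adds unscheduled visits, for example when a device fails. Hearing outcomes says that audiologic measures such as the IOI-HA "are gathered semiannually post-randomization" in this arm, whereas Table 2 shows the IOI-HA at months 12 and 20 only.
- **Text on data collection.** Data collection says, without naming an arm: "Data are collected at the local field prior to randomization (baseline T0), after 12 months (post intervention T1) and 20 months after baseline". Read alone, this puts controls at month 12 as well, which Study interventions and Table 2 do not.
- **Telephone.** Under Adherence, "Participants who miss a scheduled meeting are contacted by telephone by study staff". That is tied to a missed appointment, and controls have no appointment between baseline and month 20.

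**The concern.** An adverse event enters the record only if staff learn of it. Treated participants have more occasions on which to mention an event, and a shorter time over which to remember it. Controls have one occasion, after up to 20 months. With the same true event rate in both arms, the record would tend to be fuller in the treatment arm.

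The article sets one open-ended collection window for everyone and an arm-specific contact schedule, and does not say which recorded events may be compared. Someone preparing the final report could reasonably tabulate everything recorded, by arm, and a reader could take the resulting excess as harm from hearing aids. The record also has a use during the trial: Modifications names accidental injury as one ground on which the trial may be modified or discontinued. Neither participants nor outcome collectors are blinded, so blinding does not offset the imbalance.

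**Working it through.** The plan gives no figure for adverse events, so there is none to reproduce. Its sample size concerns quality of life and plays no part here. What can be computed is the waiting time from an event to the next scheduled contact.

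**Inputs**
- Follow-up of 20 months (Study design; Data collection).
- Control contacts after baseline: month 20 (Study interventions; Table 2).
- Treated contacts after baseline: months 12 and 20 (Study interventions; Table 2).
- Variant for the treated arm: months 6, 12, 18 and 20, if the semiannual IOI-HA is carried out as Hearing outcomes describes.

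**Assumptions (not in the document)**
- Events fall evenly over the 20 months.
- Nothing is reported between scheduled contacts, and unscheduled visits are ignored.

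**Formula.** If scheduled contacts cut the 20 months into gaps g, an event falls in a gap with probability g/20 and then waits g/2 on average. The mean delay is the sum of g²/2 over the gaps, divided by 20.

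| Schedule | Gaps (months) | Mean delay (months) | Longest gap (months) |
|---|---|---|---|
| Control: 20 | 20 | (400/2)/20 = 10.0 | 20 |
| Treated: 12, 20 | 12, 8 | (144/2 + 64/2)/20 = (72 + 32)/20 = 5.2 | 12 |
| Treated: 6, 12, 18, 20 | 6, 6, 6, 2 | (18 + 18 + 18 + 2)/20 = 2.8 | 6 |

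The mean wait in controls is about twice that in treated participants (10.0/5.2 = 1.9). Unscheduled visits would shorten the treated wait further. If controls were in fact contacted at month 12, as the Data collection sentence can be read, their mean would also be 5.2 months and the scheduled imbalance would disappear. The sections therefore need to agree.

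**From delay to bias.** With no true difference, the ratio of recorded events equals the ratio of the proportions captured in each arm. The document gives no capture proportion, event rate or recall information, and does not say whether booster or unscheduled visits ask about adverse events. The direction is predictable (fuller capture in the treated arm); the size is not calculable.

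**Outcomes not affected.** Table 2 schedules hospitalisations and falls in both arms at T0 and T2. Both arms are asked at the same times, so the unequal contact count does not enter these outcomes as scheduled.

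**The case against.** The strongest reply is that the article plans no between-arm analysis of adverse events. They are neither a primary nor a secondary outcome, and Statistical analysis names no test for them. Recording and notification serve participant protection, and the harms of most comparative interest, hospitalisations and falls, are already collected equally. This stands. A reader might infer that a planned comparison is biased; the document contains none. The point concerns only a by-arm tabulation of everything recorded, which the article neither plans nor rules out.

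A reader might also infer that serious events in controls will reach the review board up to 20 months late. That is the worst case: an event just after baseline that nobody reports. A condensed article commonly leaves reporting routes and time limits to the full protocol, and Consent and confidentiality provides treatment and compensation for accidental injury during the trial, which may prompt reports between visits. The document does not support a claim that control events would go unnoticed until month 20. Spontaneous reporting would not, however, make active contact equal between the arms.

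Finally, the expected risk is stated to be low, controls receive no device, and more contact with those who do is a defensible choice. This limits the weight of the point. It does not make the two records comparable.

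**Conclusion.** The point holds in a limited form. The article promises adverse event collection in both arms to study end, on a schedule that gives controls one contact after baseline and treated participants at least two, plus unscheduled visits. A table by arm of all recorded adverse events would tend to show an excess with hearing aids when there is no true difference.

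The one quantity that follows from the schedule is the mean delay to the next scheduled contact: 10.0 months against 5.2 (2.8 if the IOI-HA is semiannual as written), given evenly spread events and no spontaneous reports. Any risk ratio would rest on capture rates that the document does not give, so none should be quoted. The primary outcome, the scheduled secondary outcomes and the stated analyses are untouched. This is a matter of wording and reporting, worth settling before any safety table is produced.

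**What to change.** 1. In Adverse events, state that any between-arm safety comparison uses only events solicited with the same questions in both arms at T2: the existing hospitalisation and fall items plus one all-cause adverse event question.
2. Add that question to Table 2 for both arms at T2. Record the T2 answers as given, without filling them in from interim treatment-arm records.
3. List events learned at booster or unscheduled visits descriptively, for the treatment arm only.
4. Reconcile Study interventions, Hearing outcomes, Data collection with Table 2, and Adverse events on who is contacted when, in particular controls at month 12 and the frequency of the IOI-HA.

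The cost is some wording and one added question at an existing visit. The article requires a formal amendment with prior board approval for changes to study procedures that may affect the study, which may cover the added question. The downside is that interim treated-arm events do not count in the comparison, and recall over 20 months is long in both arms. Even without the new question, items 1 and 3 work using the hospitalisation and fall items alone.

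A scripted 12-month telephone call to controls, with the same event questions put to the treated arm at its visit, would equalise the scheduled delay at 5.2 months. It is optional. It means up to 232 calls and adds questioning of controls, which the Discussion names as a possible cause of change in that arm.

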### Auditing and inspecting

PI will permit study-related monitoring, audits, and inspections by the IRB of all study related documents (e.g., source documents, regulatory documents, data collection instruments, study data). PI will ensure the capability for inspections of applicable study-related facilities.

### Patient and public involvement statements

This trial is carried out without patient or public involvement. Neither patients nor the public are involved in the development of the objective, design, or implementation of this trial. Patients will not be invited to develop patient-relevant outcomes or interpret the results, or to participate in the writing or editing of the final manuscript for readability or accuracy.

### Ethics/dissemination

#### Ethics approval and protocol amendments

The study was approved by Peking University’s Institutional Review Board (IRB00001052-19046). Any modifications to the protocol which may impact on the study, or the potential benefit and safety of the participants, including changes of study objectives, study design, participants, sample sizes, study procedures, or significant administrative aspects, will require a formal amendment to the protocol. Such amendment will be approved by the IRB prior to implementation.

#### Consent and confidentiality

Investigators will introduce the trial to participants in light of the information provided in the information sheets. Participants will then be able to have an informed discussion with the investigator. Investigators will obtain written consent from willing participants. For confidentiality, each participant will be given a unique identification number. Other identification information such as names, mobile phone numbers, and addresses will not be recorded in the same form as sensitive data. In case of any accidental injury during the trial, medical treatment and economic compensation will be provided according to the laws and regulations of China.

#### Dissemination

PI will be given access to the cleaned data sets. Results will be disseminated in the clinical and scientific communities and also to the population with hearing loss via peer-reviewed research publications both online and in print, conference and meeting presentations, posters, newsletter articles, website reports, and social media. Results will be reported according to the Consolidated Standards of Reporting Trials (CONSORT) guidelines [40]. Important protocol modifications will be reported when findings are disseminated.

## Discussion

The quality of life is associated with individuals’ physical health, psychological experience, and social relations [24]. It is relevant to multiple physical and mental diseases and social care systems [41]. Improvements in quality of life are important outcome measures for hearing treatment, both clinically and for researchers [42]. This paper describes a protocol for an RCT to evaluate the impact and cost-effectiveness of a community-based hearing aids intervention on quality of life among Chinese adults with untreated hearing loss.

This will be the first RCT accessing the efficacy of hearing aids intervention on quality of life among Chinese adults. Strengths of this study include the robust randomized controlled trial design, with randomization stratified by hearing loss severity to reduce contamination, the inclusion of follow-up measures, and the rigorous economic evaluation. This study will contribute to building the evidence base around the effectiveness of interventions to improve the well-being for Chinese adults and provide references for other countries.

We should note some weaknesses in the design of the trial. First, participants in the control group might also undergo changes in quality of life, which may conceivably be induced by questions about their health behaviors. It has been shown that participants’ behaviors can be increased or changed simply if questions are asked about their behaviors [43]. In our study, there is thus a chance that the effects of asking people about their behaviors will reduce any differences between the intervention and the control groups and thereby the possibility of finding a significant effect. The second limitation is that most data will be self-reported which are prone to bias. Therefore, we will design several corresponding questions in the questionnaires or conduct pre-test and post-test to avoid subjective bias. For example, the question about self-rated health is asked twice to verify the potential mistakes. Finally, this study is limited by being adaptable to the pragmatic realities of multi-country projects while maintaining scientific integrity, such as understanding how different health organizations work, how to observe ethics processes, how to get accurate translation of questionnaire scales, or how to gain permissions and copyright in different countries.

To conclude, whether hearing treatment and rehabilitation can delay quality of life decline in at-risk adults is lacking compelling evidence, but could have substantial clinical, social, and public health impacts for people with hearing loss. When completed in 2021, our study should provide definitive evidence of the cost-effectiveness of hearing aids treatment on quality of life in community-dwelling Chinese adults with hearing loss.

